#### Cost and cost-effectiveness analysis

In addition to estimating the costs of replicating the intervention, we will also perform a limited cost-effectiveness analysis. We will estimate the cost per additional screening completed, comparing the 3 study arms. Consistent with accepted methods of cost-effectiveness analysis, the numerator of each incremental cost-effectiveness ratio will include both intervention costs, and the costs of health care services, other than the recommended CRC screening, whose use may be attributable to the intervention. This component – attributable health care services – will be estimated by multiplying reported health care visits (measured in the 12-month participant survey) by unit cost estimates from the Medicare Physician Fee schedule. Although most study participants will not be Medicare beneficiaries, Medicare’s reimbursement methodology was developed to reflect true resource cost, thereby serving as a proxy for unit cost [44]. In sensitivity analysis, we will evaluate a range of unit cost estimates, both lower and higher than the average Medicare reimbursement level. Patient time and travel costs for medical visits will be estimated from the literature [45].

Because the measure of effectiveness in this analysis is additional screening completed, the cost-effectiveness analysis will not include the cost of screening or subsequent costs associated with CRC diagnosis and treatment. Resource utilization and cost data are typically skewed, and therefore the sample size of the trial will likely be insufficient to detect significant differences in costs between study arms [19]. Sensitivity analysis will be used to assess the impact of assumptions and uncertainty on results and conclusions [46, 47]. This analytic approach is appropriate in economic studies that “piggyback” randomized trials [48].

### Sample size and power

The primary aim involves two pair-wise comparisons of equal importance. We fix the probability of a Type I error at 0.025 for each comparison in order to maintain the overall probability of a Type I error at 0.05. We powered the study to detect a difference of 20% for each pair-wise comparison, assuming equal randomization to each of the three arms, and that approximately 20% of participants in the control arm will be adherent with recommended CRC screening. Table 5 shows the power we expect to have using two-sided Cochrane-Mantel-Haenszel tests and indicates that we should have sufficient power to detect a clinically meaningful difference even if the proportion of participants in the control arm with the primary endpoint is somewhat different than we expect.

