
### Study participants

#### Eligibility

We plan to enroll 315 participants on the study. To confirm eligibility, participants will complete an eligibility survey. Participants must meet the following criteria in order to enroll on the study: 1) have previously enrolled in CCSS, 2) age > 30 years old, 3) were treated with radiation to the abdomen, pelvis, spine, or total body irradiation, 4) no history of CRC, 5) no family history of CRC, 6) have not had a colonoscopy in the last 5 years or multitarget stool DNA test in the last 3 years, 7) have a smartphone, 8) reside in the United States, and 9) speak English.

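### Testing both primary comparisons at a fixed 0.025 gives up power that a Holm step-down would recover at the same 0.05 family-wise error

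*Protocol article*

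**What the plan says.** The Protocol article, under Sample size and power, states: "The primary aim involves two pair-wise comparisons of equal importance". It continues: "We fix the probability of a Type I error at 0.025 for each comparison", and gives the reason: "in order to maintain the overall probability of a Type I error at 0.05". Power is computed "using two-sided Cochrane-Mantel-Haenszel tests", for a 20-point difference in each comparison, with about 20% of controls screened and equal allocation. The Primary efficacy analysis section compares each intervention arm with control by the same test. Neither section lets the level of one comparison depend on the result of the other, so the stated rule is a non-sequential Bonferroni split.

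**The concern.** The only reason given for 0.025 is to hold the overall error at 0.05. With two hypotheses, Holm's step-down meets that aim at least as well:

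- If both nulls are true, any false rejection requires the smaller p-value to be at or below 0.025. By the Bonferroni inequality this has probability at most 0.05.
- If only one null is true, it can be rejected only if its own p-value is at or below 0.05, so the error is again at most 0.05.

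Neither step assumes anything about dependence, so the shared control arm is no obstacle. No hierarchy is needed either, which suits comparisons of equal importance.

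The loss falls on the second claim. The arms are nested: one adds text messages to the control resources, and the other adds provider materials to that. Unequal true effects are therefore plausible, and the fixed split costs the weaker arm most.

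**Working it through.** **Inputs.** Total sample size: "We plan to enroll 315 participants on the study" (Eligibility). Allocation: "assuming equal randomization to each of the three arms", so 315 / 3 = 105 per arm. Effect: "We powered the study to detect a difference of 20% for each pair-wise comparison". Control rate: "approximately 20% of participants in the control arm will be adherent with recommended CRC screening", so 20% against 40%.

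**The plan's own figure.** 0.025 + 0.025 = 0.05, as stated. The stated power is in Table 5, which is not shown, so it could not be checked.

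**Power of one comparison, normal approximation.**
Power = Φ{[Δ − z·√(2p̄(1−p̄)/n)] / √[(p₀(1−p₀) + p₁(1−p₁))/n]}, with n = 105, Δ = 0.20, p̄ = 0.30.

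- Standard error under the null: √(0.42/105) = 0.0632. Under the alternative: √(0.40/105) = 0.0617.
- Two-sided 0.025 (z = 2.241): (0.20 − 0.1418)/0.0617 = 0.944, power 82.7%.
- Two-sided 0.05 (z = 1.960): (0.20 − 0.1240)/0.0617 = 1.232, power 89.1%.

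At 0.025, 80% power needs 99 per arm, or 109 with a continuity correction, so 315 is consistent with about 80% power per comparison.

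**Fixed split against Holm.** Each scenario used 1,000,000 simulated three-arm trials with a shared control (correlation of the two test statistics about 0.49 to 0.50) and a two-sided single-stratum Mantel-Haenszel test without continuity correction. Rates are control / arm 1 / arm 2, and n is 105 per arm unless noted. Each cell gives fixed split → Holm.

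| True rates | Arm 1 | Arm 2 | Both | At least one |
|---|---|---|---|---|
| 20/40/40 | 83.0 → 87.2% | 83.0 → 87.2% | 72.8 → 81.3% | 93.1% either way |
| 20/35/40 | 58.0 → 66.9% | 83.0 → 85.2% | 53.3 → 64.4% | 87.7% either way |
| 20/30/40 | 28.2 → 37.9% | 82.9 → 83.6% | 27.0 → 37.3% | 84.1% either way |
| 15/35/35 | 87.7 → 91.4% | 87.6 → 91.3% | 79.5 → 86.9% | 95.8% either way |
| 25/45/45 | 79.5 → 84.2% | 79.4 → 84.2% | 67.8 → 77.2% | 91.2% either way |
| 20/40/40, 84 per arm | 73.1 → 78.4% | 73.0 → 78.4% | 59.3 → 69.9% | 86.9% either way |

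The 84 per arm is an assumed 20% loss (105 × 0.8); the document gives no attrition rate.

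**Consistency check, first row.** Arm 1 plus arm 2 minus both should equal at least one. Fixed split: 0.8296 + 0.8296 − 0.7279 = 0.9313. Holm: 0.8722 + 0.8725 − 0.8134 = 0.9313.

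**Error control.**
- Both arms null at 20%: family-wise error 4.7% under either rule.
- One arm null, the other at 40%: the null arm is falsely rejected in 2.5% of trials under the fixed split and 4.3% under Holm, still below 5%.

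**Equivalent sample size.** With the formula above at two-sided 0.025, n = 118 gives (0.20 − 0.1337)/0.0582 = 1.138, power 87.2%. Matching Holm's per-comparison power under the fixed split would thus take about 118 × 3 = 354 participants, 39 more than planned.

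**The case against.** The fixed split is valid, meets its stated aim exactly and gives about 83% power on the protocol's own metric, which is power per comparison. The protocol never claims power to show both effects. On its own metric the gain is about 4 points, and the chance of at least one success does not change. All of that is correct, and it makes this a matter of efficiency.

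Two costs are also real:

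- **Per-comparison error.** The fixed split holds each comparison at 0.025 whatever the other arm does. Holm does not: the rate for an ineffective arm rises to 4.3% when the other arm works, and under the global null the expected number of false rejections goes from 0.050 to 0.054. The protocol justifies 0.025 only by the overall error, however, and that is still controlled.
- **Intervals.** The primary analysis also estimates a stratum-weighted difference. Under the fixed split, 97.5% intervals agree closely with the decisions. Under Holm, a second success with a p-value between 0.025 and 0.05 will usually have a 97.5% interval that includes zero. These are exactly the trials in which Holm helps: 81.34 − 72.79 = 8.55% of trials at 20/40/40, and 64.39 − 53.30 = 11.09% at 20/35/40. This is a sound reason for some to keep the split, but reporting can deal with it.

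The absence of a separate analysis plan does not weaken the point, because the protocol itself fixes the rule.

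**Conclusion.** The concern holds as a worthwhile, low-cost improvement; the plan contains no error here. On the protocol's own criterion, overall error of 0.05, Holm dominates the fixed split without extra participants. At the design effect the gain is about 4 points per comparison and 8.5 points for showing both. When one arm is weaker, that arm gains about 9 to 10 points.

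The superiority of Holm over the split is exact. The size of the gain assumes 105 evaluable participants per arm, rates that do not differ between the two age strata (stratum shares and rates are not given), and the design rates or the alternatives tabulated. With 84 evaluable per arm the gain for showing both is larger, at 10.6 points (69.9 − 59.3).

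**What to change.** Before outcome data are seen, state in the Primary efficacy analysis and Sample size and power sections, and in the analysis plan, that the smaller of the two p-values is tested at 0.025 and, if significant, the larger is tested at 0.05. A step-down Dunnett procedure is an alternative, since the control arm is shared. Restate the power under the chosen rule, per comparison and for both.

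Keep 97.5% confidence intervals for both differences, and say in advance that the step-down test decides significance and that an interval may include zero when the second comparison is significant. The cost is one sentence in each document, a recalculated power table and that reporting note. The sample size can stay at 315.

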**Table 5 Tab5:**
[figure not shown]
Power to detect a difference between intervention and control arms

## Discussion

We describe the first Type II Hybrid Implementation Study to our knowledge to test the efficacy of a mHealth intervention to improve CRC screening in childhood cancer survivors at high risk for CRC due to previous exposure to radiation to the abdomen, pelvis, spine, or TBI. The importance of this study cannot be understated in that cancer survivors with this radiation exposure are almost four times more likely to develop CRC, a preventable cancer, compared to the general population [6].

### Limitations and anticipated challenges

There are several limitations to this protocol. The burden to understand the effectiveness of the mHealth intervention requires robust participation among the PCPs of enrolled patients and their interest in reviewing the study materials and completing the questionnaires and interviews. While PCPs generally value research and consider it an important pathway towards the generation of useful clinical knowledge, they also find it to be administratively burdensome [49]. Based on feedback from our PCP Advisory Board on how to best address this potential issue, we have ensured that all PCP study materials are concise, have included a gift card for participation in each study component, and have developed a structured follow-up plan to collect any missing data.

We also recognize that apprehension about the cost of CRC screening may impact the willingness of participants to follow through with their screening. Previous studies indicate that concern about cost is a leading patient-reported barrier to CRC screening [50, 51]. Since many insurance companies are unaware that people at high-risk for developing CRC should begin screening when they are 30 years old, it is possible that younger participants could have a high out-of-pocket cost for this screening. To address this challenge, we provide all participants with a templated insurance letter they can use to communicate why CRC screening should be covered by their insurance company. As part of their study materials, we also supply participants with a resource which lists organizations that provide financial assistance for CRC screening. In addition, participants in the intervention arms receive a video about CRC screening cost as part of the text-message intervention.

### Potential for impact and implications

There is a critical need to increase the rate of CRC screening among high-risk cancer survivors. This study will advance our understanding of CRC prevention within the high-risk childhood cancer survivor population by evaluating both the effectiveness of an mHealth intervention and assessing implementation strategies that facilitate or impede intervention outcomes. The study design -a three-arm, hybrid type II effectiveness and implementation trial- will inform the development of specific implementation strategies for the post scale-up of this study and will provide generalizable, comprehensive, and clinically useful data for decision makers to ensure future sustainability.

## Data Availability

Not applicable.

## Abbreviations

ANOVA: Analysis of variance
APRN: Advanced Practice Registered Nurse
ASPIRES study: Activating Cancer Survivors and their Primary Care Providers to Increase Colorectal Cancer Screening Study
BSI: Brief symptom inventory
C: Control
CCSS: Childhood Cancer Survivor Study
CFIR: Consolidated Framework for Implementation Research
COG: Children’s Oncology Group
CRC: Colorectal cancer
mHealth: Mobile health
PA: Patient activation
PAM: Patient Activation Measure
PCP: Primary care provider
PROMIS: Patient-Reported Outcomes Measurement Information System
RT: Radiation Therapy
SIR: Standardized Incidence Ratio
SMN: Subsequent malignant neoplasms
SPN: Subsequent Primary Neoplasm
SCP: Survivorship Care Plan
TBI: Total Body Irradiation
